## Abstract

**Background:**

Spinal cord stimulation (SCS) is an effective method to treat neuropathic pain; however, it is challenging to compare different stimulation modalities in an individual patient, and thus, it is largely unknown which of the many available SCS modalities is most effective. Specifically, electrodes leading out through the skin would have to be consecutively connected to different, incompatible SCS devices and be tested over a time period of several weeks or even months. The risk of wound infections for such a study would be unacceptably high and blinding of the trial difficult. The PARS-trial seizes the capacity of a new type of wireless SCS device, which enables a blinded and systematic intra-patient comparison of different SCS modalities over extended time periods and without increasing wound infection rates.

**Methods:**

The PARS-trial is designed as a double-blinded, randomized, and placebo-controlled multi-center crossover study. It will compare the clinical effectiveness of the three most relevant SCS paradigms in individual patients. The trial will recruit 60 patients suffering from intractable neuropathic pain of the lower extremities, who have been considered for SCS therapy and were already implanted with a wireless SCS device prior to study participation. Over a time period of 35 days, patients will be treated consecutively with three different SCS paradigms (“burst,” “1 kHz,” and “1.499 kHz”) and placebo stimulation. Each SCS paradigm will be applied for 5 days with a washout period of 70 h between stimulation cycles. The primary endpoint of the study is the level of pain self-assessment on the visual analogue scale after 5 days of SCS.

Secondary, exploratory endpoints include self-assessment of pain quality (as determined by painDETECT questionnaire), quality of life (as determined by Quality of Life EQ-5D-5L questionnaire), anxiety perception (as determined by the Hospital Anxiety and Depression Scale), and physical restriction (as determined by the Oswestry Disability Index).

**Discussion:**

Combining paresthesia-free SCS modalities with wireless SCS offers a unique opportunity for a blinded and systematic comparison of different SCS modalities in individual patients. This trial will advance our understanding of the clinical effectiveness of the most relevant SCS paradigms.

**Trial registration:**

German Clinical Trials Register, DRKS00018929. Registered on 14 January 2020.

**Supplementary Information:**

The online version contains supplementary material available at 10.1186/s13063-020-05013-7.

## Background

Spinal cord stimulation (SCS) is an effective method to treat neuropathic pain of the lower extremity. A typical SCS device transmits electric current to the posterior columns of the spinal cord through a thin, epidural electrode. This electric current interferes with physiological pain transmission; however, the exact mechanisms of pain suppression are not fully understood. The epidural electrode is wired to an extension cable leading out through the patient’s skin, where it is connected to an implantable pulse generator (IPG) during SCS testing. To minimize the risk of local wound infection and transmission of wound infections to the epidural space, testing is usually constrained to a few days. If a patient confirms substantial pain relief, the extension wire and the IPG are implanted subcutaneously in a second surgery and can be operated by the patient via remote control.

SCS has been used in the clinic for five decades; however, it is largely unknown which of the many available SCS modalities is most effective [1]. This is mainly due to the fact that it is extremely challenging to compare all the different stimulation modalities in an individual patient and during a short test phase. On the one hand, SCS devices are manufactured by different providers, are limited to certain proprietary SCS modalities, and are largely incompatible with other SCS devices. Even in the absence of compatibility issues, electrodes leading out through the skin would have to be consecutively connected to different SCS devices and be tested over a time period of several weeks/months. The risk of wound infection for such a study would be unacceptably high and blinding of the trial difficult. Several studies have compared different SCS paradigms, but these SCS modalities were limited to those available for the particular SCS device employed. For instance, Demartini et al. and De Ridder et al. compared burst and tonic stimulation [2, 3]. Duse et al., on the other hand, studied the clinical effectiveness of burst and 1 kHz SCS. Finally, other studies compared 10 kHz stimulation with traditional paresthesia-inducing SCS [4, 5] or different frequencies of SCS (1, 4, 7, and 10 kHz SCS) using the same stimulation device [6].

The PARS-trial seizes the capacity of a new type of wireless SCS device (Stimwave, Florida, USA), which was approved for SCS in recent years [7]. Consisting of an electrode with an integrated microchip and a separate miniature receiver, this setting does not require transcutaneous electrodes and can be implanted in a single, minimally invasive surgical procedure. Most importantly, SCS testing can be extended ad libitum without increasing wound infection rates.

This technological advance coincides with a second development, namely the development of paresthesia-free SCS modalities [1]. These SCS paradigms do not cause paresthesia and, in principle, cannot be distinguished by patients. Three of the most prevalent SCS paradigms are paresthesia-free: high-density stimulation (1 kHz), high-frequency stimulation at > 1 kHz, and burst stimulation (burst) [1]. High-frequency stimulation and burst are two forms of SCS specifically developed to suppress lower back pain. High density, on the other hand, stimulates at 1 kHz with high pulse width and low amplitude to produce an almost permanent suppression of neuronal activity.

Combining paresthesia-free SCS modalities with wireless SCS offers a unique opportunity for a blinded and systematic comparison of different SCS modalities in individual patients.

## Methods/design

### Aim of the study

The study aims to compare the clinical effectiveness of four SCS modalities in individual patients. SCS modalities include three prevalent paresthesia-free modalities (“burst,” “1 kHz,” and “1.499 kHz”) and placebo stimulation.

### Study design

This trial is a prospective multi-center, double-blinded, randomized, and placebo-controlled crossover trial.

### Trial sites

The PARS-trial will recruit patients at a total of 10 centers, including university hospitals and regional hospitals located throughout Germany. Given that participating centers estimated the numbers of enrolled patients to be roughly 2–3 patients/year, we opted for a higher number of hospitals to complete the study in approximately 2 years.

### Patient inclusion criteria

The trial will recruit patients suffering from intractable neuropathic pain, who have been considered for SCS therapy according to the German guidelines and, prior to the study, were already implanted with a wireless SCS device (Stimwave, Florida, USA). Inclusion criteria require placement of a single epidural electrode with the distal tip located between the 8th and the 12th thoracic vertebra. Patients with pain in the lower extremity are eligible for this trial. Pain distribution can be unilateral or bilateral. Patients with concomitant lower back pain are eligible too, as long as pain in the lower extremities predominates. Duration of pain history should be longer than 6 months and shorter than 5 years. This choice was based on a study by Kumar et al. [8] which assessed the impact of wait times on spinal cord stimulation therapy outcomes. The authors came to the conclusion that best outcomes were achieved within the first 5 years after symptom onset. In addition, our trial only considers patients who have been found eligible for SCS therapy according to the German guidelines and with pain symptoms persisting for at least 6 months.

The trial will exclusively include adults (≥ 18 years of age) who provide written informed consent after (a) receiving detailed information pertaining to the trial (including a detailed patient information brochure which was approved by the local ethics committee), (b) having at least 24 h to consider trial participation, and (c) having no further questions at the time of consent. Only dedicated study physicians who have been trained and authorized by the principal investigator will recruit patients and/or gain informed consent. None of the physicians involved in the initial treatment, i.e., implantation of the wireless SCS device, will be involved in recruiting patients and/or gaining informed consent. Patients will be approached after implantation of a wireless SCS device by study physicians who will explain the study in detail. Should the patient consider study participation, he or she will be handed a detailed information sheet which has been reviewed and approved by the local IRB. All patients must be able to understand the nature and the extent of the trial.

### Patient exclusion criteria

Exclusion criteria include coverage of pain area of less than 90% during intraoperative testing (using paresthesia-inducing stimulation). Patients suffering from other pain syndromes such as ischemic pain (e.g., peripheral artery disease) and primary chronic pain will not be included in the trial. Exclusion criteria further include coagulopathy, pregnancy, neurodegenerative disease, lack of understanding of the trial, and any planned changes in existing pain medication for the duration of trial participation. We opted against exclusion criteria based on age limit but rather included neurodegenerative disease and lack of understanding of the trial as exclusion criteria to better reflect the biological age of patients.

### Patient withdrawal criteria

Patients can revoke their consent to participate in the trial at any time, in writing or verbally and without giving reasons for their decision. Patients who revoke their consent can decide whether their trial data should be included in the final analysis. Individual termination criteria with regard to trial participation include withdrawal of the patient’s consent to participate in the trial, severe wound infection leading to explantation of the SCS device, and any type of morbidity or patient discomfort leading to explantation of the stimulator.

### Assignment of intervention, randomization, and blinding

The study is planned as a fourfold crossover study using a Williams design. In a crossover design, patients are not randomly assigned to treatments, but rather treatment sequences are randomized. Such a crossover design avoids inter-patient variability and reduces the required sample size to power this trial. On the other hand, it increases the length of the intervention for each individual patient and thus, ultimately, might negatively influence patient compliance.

Since some part of the SCS effect observed at early stages of therapy may be the result of a placebo effect, and some studies have reported placebo effects comparable to SCS effects [9], the study also includes a placebo control, i.e., a time interval in which there is no stimulation and which should be indistinguishable from paresthesia-free SCS.

Each patient is treated with four SCS modalities (“burst,” “1 kHz,” “1.499 kHz,” and “placebo”). All stimulation sequences are generated at the beginning of the trial, and each patient will be randomly assigned to one of 24 unique treatment sequences. An independent technician will program the SCS modalities as well as the order of the different stimulation modalities into the wireless SCS control hardware prior to the intervention.

A randomization list was generated prior to trial initiation. The designated trial statistician had no access to the lists and was not involved in the generation of the randomization list. A randomization number (1–500) was randomly assigned to one of the 24 unique treatment sequences (e.g., randomization #1: “1 kHz”-“placebo”-“1.499 kHz”-“burst,” randomization #2: “burst”-“placebo”-“1 kHz”-“1.499 kHz”). This list was further divided into blocks of equal length so that each participating center would receive a list of randomized sequences and a matching number of sealed envelopes containing one treatment sequence per envelope (e.g., center #1 would receive randomization numbers and the corresponding treatment sequences 1–50 as well as 50 sealed envelopes with treatment sequences 1–50, center #2 would receive randomization numbers and the corresponding treatment sequences 51–100, as well as 50 sealed envelopes with treatment sequences 51–100).

The following procedure is applied for allocation: patients are screened and enrolled at each center. Study personnel will remove sealed randomization envelopes from the investigator site file. Sealed randomization envelopes are then handed out to an independent technician who opens the randomization envelope and uses the treatment sequence to program the wireless SCS device.

Study participants and physicians will be blinded to the order of the four stimulation modalities. The four different stimulation modalities will only be known to these two parties as programs 1–4. In coordination with the study center, patients will use the remote control of their SCS device to select the pre-set programs in consecutive order. There will be no contact with the independent technician for the duration of trial participation (35 days), and study personal must confirm double-blinding at the end of the study period. An emergency plan to unblind the treatment sequence was installed and can be enacted, e.g., in case the treatment sequence is required to replace a SCS device.

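### Each centre is sent the number-to-sequence list as well as the sealed envelopes, which defeats the envelopes and conflicts with the stated blinding at the centre that collects the VAS

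*Protocol article*

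**What the plan says.** All of the following is in the protocol article. The section *Assignment of intervention, randomization, and blinding* describes the supply of randomization material in a general sentence: "each participating center would receive a list of randomized sequences and a matching number of sealed envelopes containing one treatment sequence per envelope". It then illustrates this for two centres; for the first, "center #1 would receive randomization numbers and the corresponding treatment sequences 1–50 as well as 50 sealed envelopes with treatment sequences 1–50". The second centre is described in the same way for the next 50 numbers.

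The section also shows what an entry contains, for example "randomization #1: “1 kHz”-“placebo”-“1.499 kHz”-“burst". On access it says: "The designated trial statistician had no access to the lists". No other role is excluded.

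At allocation, "Study personnel will remove sealed randomization envelopes from the investigator site file", and an independent technician opens the envelope and programs the device. On blinding, "Study participants and physicians will be blinded to the order of the four stimulation modalities"; both parties are to know the modalities only as programs 1 to 4. Study personnel are asked to confirm the double blind at the end, and an emergency unblinding plan is said to exist.

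*Intervention* and *Patient timeline and trial visits* assign patient contact to the study centre. It asks for the VAS and tells the patient when to switch stimulation off and when to start the next program. *Primary endpoint* defines the outcome as the patient's own VAS rating after 120 h of stimulation.

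**The concern.** A sealed envelope protects the sequence only if its contents are not available elsewhere at the same place. Here the centre is also given those contents, indexed by randomization number. A member of staff with the list and the patient's number would know which program is placebo.

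The outcome is subjective and the comparator is no stimulation. The article itself notes that placebo effects comparable to SCS effects have been reported. Staff who know that a patient is about to start, or has just finished, the placebo program could influence expectation or reporting when they make contact. That would bear on the active-versus-placebo contrasts in particular. Blinded comparison is also the advantage the article claims for this trial.

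**Working it through.** There is no statistical figure to reproduce; the point rests on what the text says, with a little arithmetic on the list.

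**1. Is the list a separate item?** Yes. The general sentence and both centre examples name the list, or the numbers with their sequences, and then the envelopes in addition. Only the envelopes are called sealed. Three consistent statements make a slip of wording unlikely.

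**2. Do the counts agree with that reading?** The list is described thus: "A randomization number (1–500) was randomly assigned to one of the 24 unique treatment sequences". On sites: "The PARS-trial will recruit patients at a total of 10 centers". So 500 / 10 = 50 numbers per centre, which matches the ranges 1–50 and 51–100. With 60 patients planned, 60 / 10 = 6 numbers per centre would be used on average, and 50 − 6 = 44 would not.

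**3. What does the list reveal?** Four modalities can be ordered in 4 × 3 × 2 × 1 = 24 ways. Placebo holds any given position in 3 × 2 × 1 = 6 of them. If the 24 sequences are equally likely, a guess at the placebo program is right with probability 6 / 24 = 1/4. With the list and the patient's number, it is known with certainty.

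**4. Who is where?**

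| Step | Party named in the article |
|---|---|
| Receives the list and the envelopes | Centre |
| Takes the envelope from the investigator site file | Study personnel |
| Opens the envelope and programs the device | Independent technician |
| Contacts the patient, asks for the VAS, directs program switches | Study centre |
| Fourth VAS under stimulation (day 36) | Outpatient visit at the trial site |
| To be blinded to the order | Participants and physicians |
| Said to have no access to the lists | Trial statistician |

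The party that receives the list is the party that conducts every primary assessment. The one person expressly kept from the lists does not collect the VAS.

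**5. Does anything else in the article resolve this?** No. It does not say that the list is sealed, that it goes to the technician, or that it is kept from staff who contact patients. The emergency plan concerns one patient's sequence, for instance when a device is replaced. That need does not require 50 sequences at a centre.

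**The case against.** The strongest reply is that the article names no custodian. A centre is an institution: the list could be locked away, or held by the technician, and still have been sent to the centre. Such custody would fit the blinding statements, and an article commonly leaves it to the full protocol. A restricted local list might also serve emergency unblinding, since the article rules out contact with the technician during the 35 days.

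Part of this stands. A reader might infer that the lists lie open and that staff who take the VAS have looked up the placebo program. The documents do not support that. That the list is unsealed is inferred from its contrast with the sealed envelopes. Nothing says that the randomization number is visible on the envelope, that the callers are the people who handle the site file, or that anyone consulted a list.

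A reader might also infer that allocation concealment is lost as it would be in a parallel-group trial. That is too strong: every patient receives all four modalities, so foreknowledge of the order cannot steer a patient towards or away from placebo. Nor is the assessor simply unblinded. The patient rates the VAS, and nothing suggests that the patient sees the list.

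What does not stand is that this is only an omitted detail. The article affirmatively describes sending number-to-sequence lists to centres. If the full protocol restricts custody, the published description is wrong and still needs correcting.

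**Conclusion.** The point holds as a defect in the stated procedure. Giving the number-to-sequence list to the centre that contacts patients, collects the VAS and directs program switches makes the sealing of the envelopes ineffective and conflicts with the blinding described in the same section.

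In scope it covers, as written, all 10 centres and all 500 entries. In effect its size is unknown: any bias would be indirect, through staff on a self-rated scale, and the article gives nothing from which to estimate it. The conclusion assumes that the article describes the supply of material correctly. It does not assume that staff used the list, and it does not support saying that every patient was in fact unblinded or that the double-blind claim has already failed.

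**What to change.** - Rewrite the supply sentence and its examples so that centres receive only opaque, sequentially numbered, sealed envelopes, used in numeric order.
- Hold the number-to-sequence list centrally or with an unblinded party such as the independent technician, outside the investigator site file. Withdraw any list that blinded site staff can reach.
- Provide emergency unblinding from that holder, one patient at a time. The used envelope cannot be relied on for this, because the technician has taken and opened it and the article does not say that it returns to the site. If the technician is the holder, the ban on contact during the 35 days needs a stated exception.
- Recruitment began in April 2020, so record for each centre whether blinded staff had access and from when, and report it as a limitation. Add an exploratory comparison by access only if numbers allow. Excluding everyone enrolled while a list was accessible could leave too few patients to be informative.

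**Cost:** a short amendment, a letter to the 10 centres and a central or technician-held route for emergency unblinding. Sample size and patient procedures do not change.

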### Methods to reduce other types of bias

All centers participating in the study will be proficient in the implantation of the wireless SCS device, i.e., have more than 1 year of experience implanting the device and/or have attended an implantation course offered by the Department of Neurosurgery at Heidelberg University Hospital. In addition, existing pain medication will remain unchanged for the duration of trial participation unless the patient’s condition requires changes in pain medication. Potential changes in pain medication will be recorded. Study participants are instructed to record each day, if there were any changes in medication. Any change of study medication within the intervention period will lead to study withdrawal.

### Intervention

Seven days after implantation of the wireless SCS device, patients are contacted by the respective study center and asked to quantify pain on the visual analogue scale (VAS) and to complete the study questionnaires (Table 1). Patients are then requested to activate the first SCS modality which is known to them only as program 1. One hundred twenty hours after activation of the first SCS modality, patients are contacted once more by the respective study center and asked to quantify pain on the VAS and complete the study questionnaires. Patients are then requested to switch off SCS. After a washout period of 70 h, patients are contacted again by the respective study center. Once more, patients are asked to quantify pain on the VAS and complete the study questionnaires. Patients are then requested to activate the second stimulation program which is known to them only as program 2. This procedure (stimulation, test battery, washout phase, test battery, activation of the next SCS modality) is repeated until patients have been consecutively treated with all four SCS modalities.

